**PROTOCOL SUMMARY**

| **Name of Company**  Laboratoire CHAUVIN | |
| --- | --- |
| **Study code number**  NAT 2 | |
| **Name of Active Ingredient**  DHA (Docosahexaenoic acid) | |
| **Title of the study**  Double-masked, randomised, parallel, comparative study of oral supplementation with DHA (Docosahexaenoic acid) versus placebo in the prevention of age-related macular degeneration | |
| **Investigator / Coordinator**  [name] [name], Créteil | |
| **Planned study duration**  4 years (3 year follow-up duration for each patient) | **Phase of development**  NA |
| Objectives To evaluate the efficacy and safety of oral supplementation with DHA versus placebo in the prevention of age-related macular degeneration | |
| **Methodology**  Randomised, placebo-controlled, double-masked, parallel, comparative study | |
| **Planned number of patients**  248 | |
| **Diagnosis and main criteria for inclusion**   - Male or female outpatients aged >55 years and < 85 years, - Having given written informed consent, - Presenting neovascular age-related macular degeneration in one eye, - With lesions of age related maculopathy (confluent and diffuse hard drusen or/and soft drusen with or without pigmentary changes or/and reticular pseudodrusen) and with minimal visual acuity of +0.3 LogMAR ( 5/10) in the fellow eye (study eye), - Likely to attend the follow-up visits during all the study period.   **Main criteria for exclusion**   - Choroidal new vessels in both eyes, - Wide central area of geographic atrophy encroaching on fovea, in the study eye, - History of other progressive ocular disease which may complicate the assessment of age-related macular degeneration (severe glaucoma, other severe retinopathy..), - Opacity precluding evaluation of retina photographs (cataract, corneal dystrophia..), - History of serious systemic disease which may prevent patient long term participation in the study (mental disorder, cancer, stroke…), - Patients treated with anticoagulants or predisposed to bleeding or haemorrhage, - History of an allergic reaction to fluorescein injection or to indocyanine green or to iodide, - Known sensitivity to DHA or vehicle, - Treatment with Maxepa or omega-3 polyunsaturated fatty acids within the previous 2 years, - Treatment with alpha-tocopherol acetate (vitamin E), - Any concomitant nutritional supplementation , - Involvement in the last 30 days in any other investigational drug study, - Drug abuse and/or excessive use of medications, - Non-compliant patients (e.g. unlikely to comply with the study protocol), - Monocular patients (for any other reason than age-related macular degeneration). | |

| **Test product, dose and mode of administration**  840 mg daily of DHA : 3 capsules per day; 2 capsules / midday and 1 capsule / evening |
| --- |
| **Duration of the treatment**  3 years for each patient |
| **Reference therapy, dose and mode of administration**  Placebo (olive oil) : 3 capsules per day ; 2 / midday and 1 /evening |
| **CRITERIA FOR EVALUATION**  **Efficacy :** Primary variable Time to occurrence of choroidal new vessels in the study eye  *(The following prognostic factors: age, history of addiction to smoking, total cholesterol and apoE genotype will be considered as well as fish intake frequency)*  **Main Secondary variable(s)**  Percentage of patients for whom new vessels occur during the study and  Change from baseline in:   - Visual acuity (ETDRS) - DHA concentration in red blood cell membrane - Drusen (number, size and area) - Retinal function (multi focal ERG)   **Safety :**   - Slit Lamp Examination results (including grading of lens opacification/LOCS II) - Fasting plasma lipoprotein profile - Adverse or unexpected events |

# 1. LIST OF ABBREVIATIONS AND DEFINITION OF TERMS

AMD Age-related Macular Degenerarion

CNV Choroidal New Vessel

DHA Docosahexaenoic acid

DNA Deoxyribonucleic Acid

EPA Eicosapentaenoic acid

ERG Electroretinogram

ETDRS Early Treatment Diabetic Retinopathy Study

HDL-C High Density Lipoprotein Cholesterol

ICG Indocyanine Green

LDL-C Low Density Lipoprotein Cholesterol

RBCM Red Blood Cell Membrane

RPE Retinal Pigment Epithelium

S Serum

TC Total Cholesterol

TG Triglycerides

WBC White Blood Cell

# 2. INTRODUCTION

Age related macular degeneration (AMD) is the most common cause of irreversible vision loss in the elderly population in Europe and the United States (1). The common features of AMD are late age of onset and decrease of central vision resulting in central scotoma and legal blindness. The earliest funduscopic finding is that of macular drusen (localized deposits of lipids and lipoproteins underneath the retinal pigment epithelium cells), retinal pigment epithelial clumping, and areas of atrophy. Two forms of AMD are usually described : exudative or atrophic (2, 3). The atrophic form is defined by the presence of degeneration in the central retinal pigment epithelium (RPE), choriocapillaris and photoreceptors resulting from the enlargement and coalescence of small areas of peri-foveolar atrophy. Choroidal neovascularization (CNV) heralds the onset of exudative macular degeneration. Occurrence of CNV is a turning point in the course of the disease, since it induces severe and irreversible complications like serous retinal detachment, edema and hemorrhage, leading to the destruction of the macular photoreceptors. Exudative AMD is responsible for almost 90% of the severe visual loss due to AMD (4). Currently available treatments are limited to laser or photodynamic therapy in some cases of exudative AMD, in order to limit the extension of CNV (3). There is no established reference preventive therapy. Therefore a major challenge facing vision researchers is to find causes and mechanisms of the disease to develop preventive therapies.

To date, etiology of AMD remains unclear. AMD appears to be a multifactorial disease. Several environmental risk factors have been evidenced, including smoking, elevated serum cholesterol levels and systemic hypertension (1). However, a number of studies suggest that AMD has a familial component and that genetic factors contribute to its development. The 4 allele of the gene coding for apoE (an apolipoprotein involved in the transport of cholesterol and lipids) has been shown to have a protective effect on the occurrence of exudative AMD (soft drusen and choroidal new vessels) (1, 5). These findings evidenced the role of the metabolism of lipids in AMD and leaded us to investigate this pathway. Four recent independent epidemiological studies have shown a significant relationship between high intake of docosahexaenoic acid 22:6 omega 3 (DHA), a long chain poly-unsaturated fatty acid which is predominantly found in oily fish, and a decreased risk of neovascular AMD (6, 7, 8, 9). Furthermore, exudative AMD is less frequent in populations whose nutritional diet is rich in fish and AMD has begun to appear in Iceland or Japan with the shift to a more westernised diet (10). DHA appears to play an important role in the normal development, morphology and function of the retina (11, 12, 13,14). In animals (rats, guinea pig), dietary deficiency in omega 3 fatty acids has been associated with altered function of the retina. Interestingly, impaired vision due to a long period of DHA deprivation remains reversible with a DHA enriched diet. More recently studies in infants, prematured or not, have confirmed the essential role of DHA for the functional development of the retina in human (12 ).

The protective effect of DHA may be related to different mechanisms (15, 16). According to J. Seddon (8), the antithrombotic and hypolipidemic effects of the long chain omega3 fatty acids on the cardio-vascular system could also exert a beneficial effect on the vasculature of the choroids. Several other well known systemic effects of DHA could also play a preventive role in AMD, such as increased high density lipoproteins (HDL), decreased triglycerides (TG), increased apoE, anti-inflammatory role and protective effect on altered tissues such as in myocardium after ischemia reperfusion injury. This last effect, which may imply intracellular regulation as well as plasma membrane remodelling, is assumed to underlay the reduction in sudden death after myocardial infarction seen in large randomized control trials. Moreover, in the Gissi-Prevenzione trial (17, 18), omega 3 fatty acids supplied during 3.5 years reduced significantly (- 20%) overall mortality in myocardial infarction survivors, whom mostly correspond in age and sex to the population of subjects affected by age-related macular degeneration ( 55 years old). Finally a recent study comparing omega 6 and omega 3 supplementation in patients with carotid atherosclerosis has shown that indeed omega 3 incorporate into the arterial lesion and stabilize atherosclerotic plaques, in part by reducing its proliferative and inflammatory components (19). Therefore one might expect that once omega 3 fatty acids are incorporated into a human cell membrane they may exert their protective action locally.

Furthermore DHA is known to have specific retinal effects that are likely to play a preventive role in AMD, such as increase mitochondrial activity, increase RPE acid lipase activity, anti-oxydative , anti-proliferative and anti-apoptotic effects (20). DHA represents the main component (> 50%) of the lipids of the external membrane of the photoreceptors cells, suggesting a major role in the maintain of the structure of these cells. On the opposite, an imbalance of the lipidic composition of the retina leads to the degradation of the photoreceptors, and accumulation of deposits of debris made of lipids and lipoproteins, localized at the level of retinal pigment epithelium cells. Since photoreceptor outer segments have a high DHA content and require a constant supply of these omega 3 fatty acids due to their continuous renewal, diets rich in DHA may improve retinal function and protect against the development of exudative AMD (6, 8).

From a safety point of view, the only known side effects of omega 3 fatty acids are digestive intolerance and a modification of biochemical parameters related to platelet aggregation in human consuming very high quantities of omega 3 fatty acids. Numerous studies on omega 3 supplementation performed in the cardiovascular area involved thousands of patients without any significant side effects, particularly no haemorrhagic side effects. In the Gissi-Prevenzione study, 5000 patients aged 50 years or above had no increase in fatal or non-fatal stroke while they received PUFA together with aspirin. The American Food and Drug Administration (FDA) performed a comprehensive evaluation of more than 2600 articles on docosahexaenoic and eicosapentaenoic acids (DHA and EPA), the two long chain poly-unsaturated omega-3 fatty acids found in fish oil. The FDA concluded that dietary intakes of up to 3g daily of DHA and EPA were GRAS [generally recognized as safe] (21).

The safety profile of PUFA has been a strong argument to conduct a study with a nutritional supplement in elderly subjects who are often poly-medicated and more prone to adverse side effects with classical lipid-lowering drugs.

Recently, DHA was given in patients affected with inherited retinitis pigmentosa, an inherited retinal degeneration. A slowing of the retinal degeneration was observed (visual function analyzed by ERG features) compared with the control group. No systemic nor retinal side effect was observed (22). Moreover, a preliminary study called NAT-1 was performed in thirty-eight patients affected with an homogeneous subgroup of AMD without CNV. Among them, 22 patients were orally given DHA at the dose of 480 mg per day in combination with EPA for 6 months. Neither adverse effect nor dropout were observed. It was shown that oral intake of DHA can significantly increase the levels in serum and red blood cell membranes, even in the elderly population (23). It is now interesting to evaluate the potential efficacy of oral supplementation of DHA in preventing the occurrence of new vessels in patients affected with AMD.

# 3. STUDY OBJECTIVES

The objective of the study is to evaluate the efficacy of an oral supplementation with DHA versus placebo in the prevention of the progression of early stages of AMD. The occurrence of choroidal new vessels in AMD patients will be evaluated as a primary criterion while the progression of drusen will be considered as an important secondary criterion.

A secondary purpose is also to confirm the safety of this new treatment.

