### 6.1.2 Examination schedule

The different visits will take place on D0, Month 6 (15 days), Year 1( 30 days),

Year 2 (30 days) and Year 3 ( 30 days).

Before inclusion, a baseline assessment will take place on D0. Besides validating the inclusion and exclusion criteria, this baseline visit will also enable the recording of demographic (including ethnicity) and baseline data. Data concerning some identified risk factors for AMD, as age and history of addiction to smocking, will be recorded. Moreover a diet questionnaire must be completed in order to assess the patient’s fish intake frequency.

Any general pathology (particularly diseases predisposing to bleeding or haemorrhage) and ocular pathology as well as any concomitant treatment will be recorded.

These data will be updated all along the study.

For patients previously supplemented with omega-3 fatty acids the corresponding stopping date will be recorded.

On each visit, ophthalmic assessments will include the following:

- Best corrected visual acuity measured with ETDRS charts
- Slit Lamp Examination
- Multifocal ERG (except on 6 month visit)
- Fundus photographs
- Fluorescein angiography (except on 6 month visit)

Moreover a complete profile of blood lipids will be performed on D0, at the 6 month visit and at the 3 year visit : fasting plasma lipoproteins [triglycerides (TG), total cholesterol (TC), HDL-C and LDL-C ] and fatty acids in serum and in red blood cell membranes (RBCM) will be measured. To this end 15 ml of venous blood will be collected after a 12 hour fasting period (as described in appendix I.D).

These data will allow first to evaluate for each patient the compliance to the treatment (DHA level in plasma) and the efficacy of DHA to penetrate the cell membrane (DHA level in RBCM), then to confirm the safety of the treatment concerning the metabolism of lipoproteins (fasting plasma lipoprotein profile).

Moreover since TC is considered as a risk factor for age-related macular degeneration, it will be considered for evaluation of treatment efficacy.

Furthermore, as previously mentioned (see section 4.2), apoE genotype of consenting patients will be evaluated on DNA of white blood cells, on D0.

10 ml of venous blood will be collected. The protocol for extraction of DNA from white blood cells and for evaluation of apoE allele is given in appendix I.E. If appropriate, the efficacy of the treatment will be assessed considering the apoE genotype .

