# 8*.* STATISTICAL ANALYSIS

## 8.1 Methods

Analysis population

Three populations will be defined for the purposes of analysis.

Safety population

This comprises all patients randomised who had taken at least one unit of study medication.

Intent-to-treat (ITT) population

This comprises all patients in the safety population . The full analysis set arising from this population will comprise all available data from these patients, thus patients for whom there is no post-baseline data will not contribute to this data set.

Per-protocol (PP) population

This comprises all patients in the intent-to-treat population who did not deviate from the protocol in any way likely to seriously affect the primary outcome of the study.

The patients in each analysis population will be agreed on blind as to the treatment received and before statistical analysis begins.

The analysis of the primary efficacy variable will be performed on both the intent-to-treat and per-protocol populations.

The objective of the trial is to show the superiority of DHA versus placebo in preventing the occurrence of new vessels in patients with AMD.

STATISTICAL METHODS

All analyses will be carried out using SAS version 8.2 for PC. Tables and listings will be output directly for use in Word.

All data will be listed in individual patient listings.

Missing data will not be extrapolated.

Efficacy variables

The ocular criteria will concern systematically the study eye i.e. the eye not affected with CNV before entering the study.

The primary efficacy criterion is the time to occurrence of new vessels.

Secondary efficacy criteria:

- Percentage of patients for whom new vessels occur during the study,
- Change from baseline in visual acuity in LogMar units (ETDRS) and proportion of patients with a visual acuity decrease from baseline of more than 15 letters at ETDRS,
- Change from baseline in visual function (assessed with a multifocal ERG),
- occurrence and progression of drusen (number, size and area),
- DHA concentration increase in red blood cells membrane

Safety variables

The ocular criteria will concern both eyes.

- Slit Lamp Examination

- Profile of plasma lipoproteins

- Adverse or unexpected events

Other variables

Other variables recorded consist of demographic and baseline variables as well as history.

Concomitant medication, both systemic and ocular will be recorded.

Compliance to study drugs will be recorded as “yes” or “no” at each visit.

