At each follow-up visit, the percentage of patients with changes (from the previous assessment) in the slit lamp examination will be compared between groups by means of a CHI square test or a Fisher test .

Change from baseline in profile of plasma lipoproteins will be compared between groups using a Student t-test or a Wilcoxon Rank Sum test depending on data normality.

Adverse or unexpected events will be counted and described by visit. In case of a sufficient number of adverse events, the percentage of patients having at least one adverse event will be compared between the 2 groups by means of a CHI square test. In case of serious adverse events, these will be counted and described completely and the corresponding patient profile will be detailed.

Other variables

The comparability of quantitative parameters between groups on D0 will be analysed by a Student t-test or a Wilcoxon Rank sum test depending on data normality. Qualitative parameters will be analysed by a CHI square test or a Fisher test depending on the number of patients in classes.

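### The protocol aims to confirm safety, but its only adverse-event comparison is a conditional test of any event, which barely registers the bleeding and digestive events it singles out

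*Protocol*

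**What the plan says.** The protocol words its safety aim in two ways. Section 3 states "A secondary purpose is also to confirm the safety of this new treatment". Section 6.1.2 says that the blood lipid data serve "then to confirm the safety of the treatment concerning the metabolism of lipoproteins (fasting plasma lipoprotein profile"). The Protocol Summary is more modest: "To evaluate the efficacy and safety of oral supplementation with DHA versus placebo in the prevention of age-related macular degeneration".

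The only hypothesis stated concerns efficacy: "The objective of the trial is to show the superiority of DHA versus placebo in preventing the occurrence of new vessels in patients with AMD" (section 8.1). Section 8.2 sizes the trial on choroidal new vessels (CNV) alone.

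Section 8.1 fixes the safety analysis as follows:
- **Adverse events, default:** "Adverse or unexpected events will be counted and described by visit".
- **Adverse events, comparison:** "In case of a sufficient number of adverse events, the percentage of patients having at least one adverse event will be compared between the 2" (the sentence ends by naming the arms and a chi-square test). No figure is given for what counts as sufficient.
- **Serious events:** "In case of serious adverse events, these will be counted and described completely and the corresponding patient profile will be detailed".
- **Slit lamp, tested at every visit after baseline:** "the percentage of patients with changes (from the previous assessment) in the slit lamp examination will be compared between groups by means of a CHI" (the sentence goes on to allow Fisher's test).
- **Lipoproteins:** change from baseline is compared by a t-test or a Wilcoxon test.

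Section 6.2.2 names digestive and bleeding events as the systemic events to watch. It adds that no simple laboratory index predicts bleeding risk, so recorded events are the only bleeding signal. Section 5.5.1 permits aspirin. Section 8.1 gives neither type of event a comparison of its own.

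**The concern.** The stated aim and the fixed analysis do not match. A test of no difference can show that harm differs between groups. It cannot confirm that harm is absent or small, because a non-significant result may only reflect few events.

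The adverse-event rule has two further weaknesses. Whether any comparison is made depends on the data through an undefined condition, so with few events the reader gets no between-group estimate from this rule. When the comparison is made, it pools every kind of event over three years in patients aged 55 to under 85. Many such patients will report something, and a change in one uncommon event is diluted in the total.

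At stake is the safety statement for a product intended for years of preventive use. The primary efficacy result is not affected.

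**Working it through.** **Inputs from the protocol.** There are 248 patients, 124 per group (section 8.2). The safety population is all randomised patients who took at least one unit (section 8.1), so patients who drop out stay in the adverse-event denominator and 124 per arm is the right size. The two-sided 5% level is stated in section 8.2 for efficacy and is assumed here for the safety tests. The protocol gives no harm rates, so every rate below is an assumption and a range is shown.

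**The plan's own figure.** The only sizing figure is 245 in total, for CNV. Risks of 30% and 15% at 3 years give hazards of −ln(0.70)/3 = 0.119 and −ln(0.85)/3 = 0.054 per year, a ratio of 0.456. The Lachin-Foulkes log-rank formula with 1-year accrual, 4 years in total and 20% drop-out per 3 years gives 244, which matches. No safety quantity enters this calculation.

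**Step 1: the planned pooled test.** Assume 60% of placebo patients have any event, 5% bleed, and other events are independent of bleeding.
- Rate of other events: 1 − (1 − 0.60)/(1 − 0.05) = 0.579.
- Pooled rate if bleeding doubles to 10%: 1 − (1 − 0.579)(1 − 0.10) = 0.621, a shift of 2.1 points.
- Standard error of the difference: √(2 × 0.6105 × 0.3895/124) = 0.0619.
- Power in the direction of harm: Φ((0.0211 − 1.96 × 0.0619)/0.0619) = Φ(−1.62) = 5.3%. Adding the opposite tail (1.1%) gives about 6%. Exact enumeration gives 6.2%.

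That is scarcely above the 5% false-positive rate. With an any-event rate of 40% or 80%, power in the direction of harm is 7% or 4%. The case most favourable to the pooled test is that none of the additional bleeders has any other event. The rate then moves by the full 5 points, from 60% to 65%, and power is Φ((0.05 − 1.96 × 0.0615)/0.0614) = Φ(−1.15), about 13%.

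**Step 2: would an event-specific test of difference be enough?** Worked case, 5% against 10%: the pooled standard error is √(2 × 0.075 × 0.925/124) = 0.0335 and the unpooled one is √((0.05 × 0.95 + 0.10 × 0.90)/124) = 0.0333. Power is Φ((0.05 − 1.96 × 0.0335)/0.0333) = Φ(−0.47) = 32%. Exact enumeration of the uncorrected chi-square test at 124 per arm gives:

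| Placebo rate (assumed) | Doubled rate | Power | Chance of missing the doubling |
|---|---|---|---|
| 2% | 4% | 13% | 87% |
| 5% | 10% | 32% | 68% |
| 10% | 20% | 61% | 39% |
| 15% | 30% | 82% | 18% |

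Power passes 50% at a placebo rate of about 8%.

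**Step 3: what an interval would show.** Take a hypothetical 10/124 against 4/124. The chi-square test gives p = 0.099. The Newcombe 95% interval for the excess runs from −1.2 to +11.3 percentage points, so the result is non-significant yet compatible with a large excess. With 0/124 events in one arm, the one-sided 95% upper limit is 1 − 0.05^(1/124) = 2.4%.

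**The case against.** Several points on the other side are sound.

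- Descriptive safety reporting, without a margin or power for harm, is usual for a secondary purpose in a trial sized on efficacy. That stands: the lack of a margin or of safety power is not an error in itself.
- Confidence intervals and tables by event category may be in the statistical analysis plan, which is not shown. That also stands, so their absence alone is not the finding. The word *confirm*, the undefined condition and the choice of the pooled test are the protocol's own text.
- The introduction rests the safety case on outside evidence and on a preliminary study, so *confirm* may mean no more than checking agreement with a known profile. This is a fair reading, but it still needs an estimate for the events named, and the pooled test does not give one.

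A reader might infer three stronger things that the documents do not support. One is that bleeding and digestive harm are formally tested for superiority; in fact they have no test of their own and can enter only the pooled comparison. Another is that a non-significant or omitted test will be taken as proof of safety; the protocol contains no such rule, and its default is description. The last is that a doubling of harm would usually be missed whatever the event; at an assumed placebo rate of 15% it would be found in 82% of trials.

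**Conclusion.** The point holds in a limited form. Sections 3 and 6.1.2 promise more than section 8.1 can deliver. The one planned adverse-event comparison is conditional on an undefined count, and it is nearly insensitive to the events that section 6.2.2 names: power is about 6% for a doubling of bleeding from 5% to 10%, and about 13% in the most favourable case. An event-specific test of difference would help, but below a placebo rate of about 8% it would still miss a doubling more often than not.

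These sizes rest on assumed event rates, 124 patients per arm, a two-sided 5% level and, for the 6% figure, independence of bleeding from other events. The slit-lamp and lipoprotein comparisons do have tests of their own and are not part of the dilution problem. This is an inexpensive improvement to the safety analysis and does not threaten the trial's main result.

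**What to change.** 1. In sections 3 and 6.1.2, replace *confirm* with *evaluate*, to agree with the Protocol Summary.
2. In section 8.1, delete the condition on a sufficient number of adverse events.
3. In its place, report the between-group difference in the proportion of patients affected, with a 95% confidence interval (exact or Newcombe), whatever the count. Do this for bleeding, digestive, serious and any adverse events.
4. Add a sentence that safety conclusions are limited to the excess harm that the upper confidence limit excludes.

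All the data are already collected, and no patients or visits are added. The cost is a few more table columns and a less favourable safety statement, because the intervals will be wide.
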